## Abstract

**Introduction:**

Delirium in critically ill adults is associated with prolonged hospital stay, increased mortality and greater cognitive and functional decline. Current practice guideline recommendations advocate the use of non-pharmacological strategies to reduce delirium. The routine use of scheduled haloperidol to treat delirium is not recommended given a lack of evidence regarding its ability to resolve delirium nor improve relevant short-term and longer-term outcomes. This study aims to evaluate the efficacy and safety of haloperidol for the treatment of delirium in adult critically ill patients to reduce days spent with coma or delirium.

**Methods and analysis:**

EuRIDICE is a prospective, multi-centre, randomised, double-blind, placebo-controlled trial. Study population consists of adult intensive care unit (ICU) patients without acute neurological injury who have delirium based on a positive Intensive Care Delirium Screening Checklist (ICDSC) or Confusion Assessment Method for the ICU (CAM-ICU) assessment. Intervention is intravenous haloperidol 2.5 mg (or matching placebo) every 8 hours, titrated daily based on ICDSC or CAM-ICU positivity to a maximum of 5 mg every 8 hours, until delirium resolution or ICU discharge. Main study endpoint is delirium and coma-free days (DCFD) up to 14 days after randomisation. Secondary endpoints include (1) 28-day and 1-year mortality, (2) cognitive and functional performance at 3 and 12 months, (3) patient and family delirium and ICU experience, (4) psychological sequelae during and after ICU stay, (4) safety concerns associated with haloperidol use and (5) cost-effectiveness. Differences in DCFDs between haloperidol and placebo group will be analysed using Poisson regression analysis. Study recruitment started in February 2018 and continues.

**Ethics and dissemination:**

The study has been approved by the Medical Ethics Committee of the Erasmus University Medical Centre Rotterdam (MEC2017-511) and by the Institutional Review Boards of the participating sites. Its results will be disseminated via peer-reviewed publication and conference presentations.

**Trial registration:**

NCT03628391

Strengths and limitations of this studyThis study is the first sufficiently powered randomised, multi-centre, double-blind, placebo-controlled clinical trial in Europe.Extensive neurocognitive testing will be conducted with a valid test battery in order to assess cognitive impairment at 3 and 12 months after intensive care unit (ICU) admission.We will assess patient and family experiences associated with delirium as a novel outcome.There are little data on the optimal haloperidol regimen in ICU patients; the maximum haloperidol dose of 15 mg/day in our study may still be subtherapeutic.Lack of true clinical equipoise among nurses and physicians regarding the use of haloperidol may hamper motivation for the study.

## Introduction

Delirium occurs in up to 80% of patients admitted to the intensive care unit (ICU)^1 2^ and is associated with greater ICU and post-ICU mortality.^2^ Cognitive dysfunction and functional decline after critical illness is common, frequently persists for months after ICU discharge and is worse among patients who experience delirium.^2 3^ The symptoms and sequelae of delirium, including fear, anxiety, disrupted sleep and post-traumatic stress disorder, may persist for months after ICU discharge. The health and societal costs of delirium are estimated to exceed $10 billion per year in the USA alone.^4^

Given the burden and costs of delirium in critically ill adults, substantial research efforts have been devoted to identify safe and effective strategies to treat it. Current evidence and practice guideline recommendations advocate the use of non-pharmacological strategies to reduce delirium, including avoidance of benzodiazepine sedation, early mobilisation and the use of sleep improvement protocols. The routine use of medication-based interventions to treat delirium, other than treatments to reduce the agitation that sometimes accompanies it, are not recommended.^5 6^ The routine use of scheduled haloperidol to treat delirium is not currently recommended given a lack of current evidence regarding its ability to resolve delirium and its symptoms, nor improve relevant short and longer-term outcomes.

At the time this protocol was finalised, two randomised, placebo-controlled trials had evaluated haloperidol for ICU delirium prophylaxis or treatment and found haloperidol use did not affect days spent with delirium, days of mechanical ventilation, nor time spent in the ICU or hospital.^7 8^ In one of these randomised controlled trials, haloperidol use was associated with less agitation.^7^ Importantly, both studies were small (a combined total of 212 patients were enrolled), the ABCDEF bundle (a multimodal ICU bundle shown to reduce delirium by 50%)^9^ was not routinely used, the effect of haloperidol on delirium-related symptoms was not evaluated and the post-ICU, longer-term outcomes were not considered. Whether the response to haloperidol was different between patients with hyperactive versus hypoactive delirium was also not evaluated. The impact of haloperidol on patients’ and families’ experiences with delirium after ICU discharge remains unknown. Whether long-term mortality is causally related to delirium or simply the persistent cognitive and functional decline associated with critical illness can only be established through a randomised trial.^10^ Moreover, the use of haloperidol in critically ill adults is not without potential safety concerns given it may prolong the QTc interval, induce extrapyramidal effects and cause oversedation. Despite haloperidol’s lack of proven efficacy and the safety concerns associated with its use, haloperidol continues to be widely used in ICUs to treat of delirium.^11^

In light of the aforementioned evidence gaps that were identified at the time this trial was conceptualised, there is a clear need for a large, multi-centre, randomised controlled trial to better define the efficacy and safety of haloperidol to treat delirium in critically ill adults. This report describes the protocol for a large, multi-centre, randomised, placebo-controlled, haloperidol delirium trial that recently started enrolling patients across multiple ICUs in the Netherlands.

## Methods and analysis

### Study design

Randomised, double-blind, placebo-controlled trial of haloperidol for the treatment of delirium in patients admitted to one of six participating ICUs in the Rotterdam area in the Netherlands. See online supplemental appendix 1 for the participating hospitals.

10.1136/bmjopen-2019-036735.supp1Supplementary data

### Study population

Consecutive adults admitted to one of the participating ICUs.

### Eligibility criteria

#### Inclusion criteria for eligibility

Age≥18 yearsAdmitted to the ICU.

#### Exclusion criteria for eligibility

Admitted to the ICU with an acute neurological diagnosis (including acute stroke, traumatic brain injury, intracranial malignancy, anoxic coma). Prior non-acute stroke or another neurological condition without cognitive deterioration is not an exclusion criterion.Pregnancy or lactation.History of ventricular arrhythmia including ‘torsade de pointes’ (TdP).Known allergy to haloperidol.History of dementia or an Informant Questionnaire on Cognitive Decline in the Elderly (IQCODE) score ≥4^12^
History of malignant neuroleptic syndrome or parkinsonism (either Parkinson’s disease or another hypokinetic rigid syndrome).Schizophrenia or other psychotic disorder.Inability to conduct valid delirium screening assessment (eg, coma, deaf, blind) or inability to speak the Dutch language.Expected to die within 24 hours or leave the ICU within 24 hours.

#### Inclusion criteria for randomisation

Delirium, as assessed with the Intensive Care Delirium Screening Checklist (ICDSC ≥4) or the Confusion Assessment Method for the ICU (positive CAM-ICU assessment), at the time of ICU admission or any ICU day after ICU admission.Written informed consent obtained from the patient or their legal representative.All eligibility *in*clusion criteria (from above) are still met.

#### Exclusion criteria for randomisation

Prolonged QT-interval (QTc >500 ms).(recent) TdP.(recent) Neuroleptic malignant syndrome or parkinsonism.Evidence of acute alcohol (or substance) withdrawal requiring pharmacological intervention (eg, benzodiazepines or alpha-2 agonist) to treat.The patient is expected to die within 24 hours or expected to leave the ICU within 24 hours.No (previously) signed informed consent by patient or representative.Current participation in another intervention trial that is evaluating a medication, device or behavioural intervention.

### Study outcomes

#### Main study outcome

ICU delirium and coma-free days (DCFDs) (up to 14 days after randomisation).

#### Secondary study outcomes

During ICU stay

Richmond Agitation Sedation Scale (RASS).Maximum ICU Mobility Scale (IMS^13^) and day of maximum IMS.Quality of sleep (Richards-Campbell Sleep Questionnaire (RCSQ)^14^ and with a visual analogue scale between 1 and 7 assessing the sleep quality according to the nurse).Use of ‘escape medication’ for hallucinations and/or agitation (including atypical antipsychotics, alpha-2 agonists, GABA agonists, opiates and ‘open-label’ haloperidol).Daily study drug dose corrected for body weight (mg/kg).Self-extubation rate, removal of invasive devices (intravenous/intra-arterial catheters, drains and tubes).Adverse drug-associated events (prolonged QTc by EKG, muscle rigidity and other associated movement disorders (Simpson Angus Scale^15^) and ventricular arrhythmias including TdP).Blood pressure will be recorded previous to and 1 hour after the first study drug dose (2.5 mg equivalent) and 1 hour after the first 5 mg equivalent.Daily respiratory status (regarding endotracheal intubation and mechanical ventilation).Time from randomisation to first resolution of delirium.Time to ‘readiness for discharge from the ICU’.

Hospital discharge

Patient and family member well-being and experiences associated with delirium during and after ICU stay with the ICU Memory Tool (ICU-MT^16^) and Delirium Experience Questionnaire (DEQ^17^).

28 days after randomisation

Mortality rate.

3 months after randomisation

Cognitive outcomes with a detailed cognitive assessment battery of validated and repeatable measures of general cognition, memory, language, processing speed, attention and executive functioning, and mood (Montreal Cognitive Assessment (MOCA),^18^ Rey Auditory Verbal Learning Test,^19^ Semantic fluency,^20^ Digit Span (WAIS-IV),^21^ Trail making tests A and B,^22^ Boston naming Test (short version),^23^ Hospital Anxiety and Depression Scale (HADS)^24^).Functional outcomes and quality of life (Short Form-36 (SF-36)^25^).Patient and family member well-being and experiences associated with delirium during and after ICU stay with the ICU-MT,^16^ DEQ^17^ and Caregiver Strain Index (CSI^26^).Post-traumatic stress syndrome in participants and family members with the Impact of Event Scale–Revised.^27^

12 months after randomisation

Cognitive outcomes with a detailed cognitive assessment battery of validated and repeatable measures of general cognition, memory, language, processing speed, attention and executive functioning, and mood (MOCA,^18^ Rey Auditory Verbal Learning Test,^19^ Semantic fluency,^20^ Digit Span (WAIS-IV),^21^ Trail making tests A and B,^22^ Boston naming Test (short version),^23^ HADS^24^).Functional outcomes and quality of life (SF-36^25^).Mortality rate.

A cost-effectiveness analysis will be performed in collaboration with the Department of Health Policy and Management of Erasmus University Rotterdam (see online supplemental appendix 2 for more detailed explanation). The tools for the secondary outcomes are mentioned in table 1 with overview of timing of assessments.

10.1136/bmjopen-2019-036735.supp2Supplementary data

**Table 1 T1:** Overview of timing of assessments, including required time investment per visit/questionnaire

Moment (months)	Neurocognitive tests	Patient and family experiences (time in min)	Functional outcomes (SF-36)	Cost-effectivity questionnaires (EQ-5D-5L, iMTA MCQ, iMTA PCQ)	Other
Enrolment					Informed consent, IQCODE-N, pregnancy test (if applicable), EKG
ICU study period (3×/day)					CAM-ICU/ICDSC, RASS
ICU study period (once daily)					IMS, RCSQ. Only when on study medication: EKG, Simpson Angus Scale
0 (discharge from hospital)		Patient: ICU-MT^15^+DEQ^15^ Family: DEQ^2^			
1				30 min	
3	45–60 min	Patient: IES-R^5^+ICU MT^15^+DEQ^15^ Family: IES-R^5^+CSI^5^+DEQ^2^	10 min	30 min	
6				30 min	
12	45–60 min		10 min	30 min	

Neurocognitive tests: Montreal Cognitive Assessment (MOCA), Rey Auditory Verbal Learning Test, Semantic fluency, Digit Span (WAIS-IV), Trailmaking tests A and B, Boston naming Test (short version), Hospital Anxiety and Depression Scale (HADS).

Simpson Angus Scale=measures muscle rigidity and other associated movement disorders.

With the exception of the neurocognitive tests, all aforementioned tools are questionnaires that can be administered at home. Real-life visits only need to be paid in order to perform the neurocognitive tests.

CSI, Caregiver Strain Index, assesses the strain experienced by the caregiver; DEQ, Delirium Experience Questionnaire, measures experiences linked to delirium; EKG, Electrocardiography; EQ-5D-5L, assesses the general health status; ICU-MT, ICU-Memory Tool, assesses the experience and memories of ICU admission; IES-R, Impact of Event Scale Revised, assesses distress linked to a traumatic experience (i.e. experiencing delirium); IMS, ICU Mobility Scale, measures mobility during ICU admission; iMTA MCQ, instituut Beleid & Management Gezondheidszorg Medical Consumption Questionnaire (healthcare use); IQCODE-N, Informant Questionnaire on Cognitive Decline in the Elderly – Dutch version; RCSQ, Richards-Campbell Sleep Questionnaire, measures quality of sleep; SF-36, Short Form-36, measures the health-related quality of life.

### Treatment of subjects

#### Investigational product

Name: Haldol (haloperidol)

Mechanism: butyrophenone-derived anti-psychotic with mainly dopamine-2 receptor antagonistic properties

Placebo consists of sodium chloride for injection. Medical staff, patients and family will be blinded to the product containing haloperidol/placebo.

#### Summary of findings from clinical studies and of known and potential risks and benefits

See: Summary of Product Characteristics in online supplemental appendix 3 and Systematic Review (online supplemental appendix 4).

10.1136/bmjopen-2019-036735.supp3Supplementary data

10.1136/bmjopen-2019-036735.supp4Supplementary data

#### Dosages, dosage modifications and method of administration

The following dosing scheme will be used: start with haloperidol/placebo (further called: ‘study drug’) 2.5 mg intravenously q8h (because of delirium screening once every 8-hour shift) and increase to a maximum dose of 5 mg intravenously q8h when delirium persists during the next 8-hour shift. Doses will be reduced (50% of dose) in the very old elderly (age ≥80 years). The study drug dose will be decreased (when dosage is 5 mg intravenously q8h) or stopped (when dose is 2.5 mg intravenously q8h) when delirium has resolved (or is un-assessable due to coma) for the next 24 hours (implying: three consecutive delirium assessments during three shifts). Dosages can be lowered also at the discretion of the treating physician in case of evident rigidity, which is in line with current routine practice. Standard clinical practice for the administration of haloperidol will be followed.

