#### Patient assessments

Rigidity will be monitored with the Simpson-Angus scale^15^ and the Barnes Akathisia Rating Scale^30^ (see ‘Secondary study endpoints’ section) for study purposes only. The QTc interval will be measured daily before the administration of the second daily (afternoon) dose using a 12-lead EKG. When the QTc interval is found to be prolonged (>500 ms or an increase from baseline (=at randomisation) of ≥60 ms^31 32^), all non-study medications having the potential to prolong the QTc will be held if clinically feasible. A Standard Operating Procedure (SOP) lists the drugs known to prolong the QTc. Eight hours later, if QTc prolongation persists, study medication will be held or tapered according to the SOP and only resumed when the EKGs (evaluation frequency increased to q8h in this situation) reveal QTc prolongation to have dissipated.

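### As the article is written, study drug can be doubled at the dose right after an abnormal EKG, because the increase rule carries no QTc condition

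*Protocol article*

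**What the plan says.** **Raising the dose.** In *Dosages, dosage modifications and method of administration*, study drug starts at 2.5 mg intravenously q8h, and staff "increase to a maximum dose of 5 mg intravenously q8h when delirium persists during the next 8-hour shift". Doses are halved at age 80 or over. The one dose discretion that the section spells out is downward: "Dosages can be lowered also at the discretion of the treating physician in case of evident rigidity". It then adds, in general terms, that standard practice for giving haloperidol applies. The abstract also ties titration to the delirium screen, but at a different pace: "titrated daily based on ICDSC or CAM-ICU positivity to a maximum of 5 mg every 8 hours".

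**Responding to QTc.** *Patient assessments* fixes the timing: "The QTc interval will be measured daily before the administration of the second daily (afternoon) dose". An alert is a QTc above 500 ms or a rise of at least 60 ms from the value at randomisation. On an alert, "all non-study medications having the potential to prolong the QTc will be held if clinically feasible". Study drug comes next: "Eight hours later, if QTc prolongation persists, study medication will be held or tapered according to the SOP". It is resumed only when EKGs show that the prolongation has gone ("evaluation frequency increased to q8h in this situation").

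**Entry limit.** A QTc above 500 ms is an exclusion criterion for randomisation.

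**The concern.** The article states both the trigger for raising the dose and the response to a prolonged QTc, but neither refers to the other. The first scheduled dose after the daily EKG falls inside the 8-hour interval in which study drug is not yet addressed. At that dose the increase rule still applies as written.

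Patient safety is at stake, not inference. The introduction names QTc prolongation as a safety concern with haloperidol. *Description and justification of route of administration and dosage* gives the susceptibility of critically ill adults to side effects as a reason for the q8h, titrated regimen. Removing other QTc-prolonging drugs on an alert while leaving study drug free to rise at the same moment does not fit that reasoning. Staff are blinded, so they cannot confine caution to the haloperidol arm. A written rule is the natural place to settle it.

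**Working it through.** The point concerns how two rules interact, so the check is a trace of the schedule. There is no figure in the plan to reproduce.

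**Inputs from the article**
- Start 2.5 mg q8h, 3 × 2.5 = 7.5 mg/day; ceiling 5 mg q8h, 3 × 5 = 15 mg/day. The step is a doubling (5 / 2.5 = 2). At age 80 or over it is 1.25 to 2.5 mg, also a doubling.
- EKG once daily, just before the afternoon dose.
- Study drug is acted on 8 hours after an abnormal EKG, if prolongation persists.

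**Assumptions for the trace:** dose slots are morning, afternoon and night; delirium persists throughout; the next afternoon EKG after the first dose is abnormal.

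**Next-shift titration (dosing section), increase at dose 2**

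| First dose | Dose 2 | Next afternoon EKG | Dose right after that EKG |
|---|---|---|---|
| Morning, 2.5 mg | Afternoon | Before dose 2 | 5 mg, the doubled dose |
| Afternoon, 2.5 mg | Night, 5 mg | Before dose 4 | 5 mg, unchanged |
| Night, 2.5 mg | Morning, 5 mg | Before dose 3 | 5 mg, unchanged |

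In the morning-start row, only non-study drugs are held before the afternoon dose. Delirium persists, so that dose rises to 5 mg. Study drug is first reconsidered at the night dose.

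**Daily titration (abstract).** If the increase comes 24 hours after the first dose, it is at dose 4. That is an afternoon dose only for an afternoon start. If titration is at a fixed clock time, the overlap occurs when that time is the afternoon dose and not otherwise. Changing the interval moves the overlap between patients but adds no QTc condition.

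**Length of the gap.** From 8 hours on, persisting prolongation leads to holding or tapering, which rules out an increase. The gap is therefore one scheduled dose per alert.

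**How many patients.** A count would need the on-treatment alert rate, the distribution of start times and the proportion up-titrated. The article gives none of these, so no count is offered.

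**The case against.** **The SOP may already cover this.** The article is a condensed account and sends study-drug handling to an SOP that is not shown. That SOP could bar increases during an alert. This stands as a condition on the point. The article, however, mentions the SOP only for the list of QTc-prolonging drugs and for holding or tapering at the 8-hour step. The difficulty comes from two rules that are stated, not from a missing detail.

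**Physicians keep their judgement.** The standard-practice clause and the investigator's right to withdraw a subject for urgent medical reasons (*Withdrawal of individual subjects*) both leave room not to escalate. A reader might infer that the protocol obliges staff to double the dose on delirium alone, or leaves nothing to stop them. The text does not support that. What stands is narrower: no written QTc rule prevents the increase.

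**A patient already on 5 mg receives 5 mg after the same EKG.** True, and the point does not contest it. The dosing rationale cites a trial of 10 mg q12h (20 mg/day) with a 550 ms cut-off, no QTc difference from placebo in a trial averaging 15 mg/day orally, and no clinically important safety concerns. A reader might infer that giving any study drug during the 8-hour step is wrong. The documents do not show that. The evidence lowers the weight of the point, but it does not address raising the dose during this protocol's own alert.

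**The entry limit is not a titration limit.** A threshold for starting treatment need not govern dose changes, and a rise of at least 60 ms is not an entry exclusion at all. The comparison shows some tension, not a contradiction.

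**A number might be tempting.** One could assume that a third of patients start in each slot and apply a guessed alert rate. *Recruitment and consent* says that delirium often appears in the evening and night, which sits poorly with equal slots. Under next-shift titration at dose 2, it would make the affected morning starts less common. The pilot (no QTc above 500 ms in 14 patients, at up to 2 mg q8h) does not supply the rate: it counts patients rather than EKGs, used lower doses and does not report rises of 60 ms or more.

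**Conclusion.** The point holds in limited form. Followed literally, the article's dosing and QTc rules allow a patient still on the starting dose to be up-titrated at the dose immediately after a QTc above 500 ms or a rise of at least 60 ms. The increase is 2.5 to 5 mg, or 1.25 to 2.5 mg at age 80 or over. This is conditional on neither the unseen SOP nor the standard-practice clause preventing it.

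The effect is one dose per alert, probably in few patients; the documents do not allow a figure. The primary endpoint, sample size and analysis are untouched, as is the 15 mg/day ceiling. It merits correction because it concerns patient safety and is cheap to close.

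The difference between daily and next-shift titration is a real but minor and separate discrepancy. The QTc point does not depend on it.

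**What to change.** Add to *Dosages, dosage modifications and method of administration* and to *Patient assessments*, and confirm in the SOP: *Study drug is not increased while the most recent QTc is >500 ms or at least 60 ms above baseline, until a repeat EKG shows that the prolongation has resolved.* The current dose and the 8-hour step stay as they are.

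The rule relies on the daily EKG and the 8-hourly re-checks already planned, so it adds no procedure. Its cost is a sentence in the protocol and SOP, and an increase delayed by 8 hours or more in a few patients.

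As a separate minor correction, state one titration interval, per shift or daily, in both the abstract and the dosing section.
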